### Blinding

Because of the high level of organizational effort involved in randomizing groups, it is not possible to blind the participants, group leaders, or study employees. The data analysis will be blinded. Thus, an independent researcher will conceal the participants’ IDs and their group assignment in the data set (i.e. relabel the variables). After all results are finalized, the independent researcher will reveal the correct group identification to the authors.

### Symptom assessment

During the intervention, participants are requested to complete online surveys to assess potential changes in the therapeutic process. More precisely, there are 15 measurement points (Table 1): at the initial stage (pre-assessment (T0)), after each group session (T1–T12 including a treatment mid-point assessment after 6 weeks (T6), and a post-assessment at the end of the intervention (T12)), after 3-month follow up (T13), and finally, after 6-month follow up (T14).

### The online group intervention

The online group intervention is manualized and consists of 12 weekly sessions each lasting 90 min. Each group has a maximum of 10 participants and is guided by a psychotherapist (or a psychotherapist in training) and a self-help counsellor who has herself or himself been bereaved by suicide. The participation is voluntary and free. Participants are allowed to skip sessions or to drop out of the program at any time.

### Development of the intervention

#### Focus groups

Three focus groups were conducted in order to develop the intervention. The composition of the groups was based on gender, age and kinship to the deceased. The minimum age was 18 years, and the time since the suicide had to be at least 1 year. The 23 recruited participants were on average 53 years old (SD 13, range 20–72) and 86% were women. Most participants had lost a child (52%), followed by a spouse or partner (24%), a parent or sibling (each 10%), or others (5%). Almost all participants had received support at the time of measurement, namely from psychotherapy (86%), self-help group (48%), a doctor (29%), pastoral care (19%), or grief counseling (14%).

The focus group participants were asked what they believed were difficulties during their grief process and what were effective strategies to find meaning in relation to the suicide. Further, they were interviewed as to which themes are relevant to be included in an Internet-based intervention. The group conversations lasted 4 h with a 1-h break and were recorded in audio format, transcribed, and evaluated with respect to important themes for a group intervention.

#### Testimonial videos

Most of the sessions start with a testimonial video in which a person bereaved by suicide talks about her or his own experiences of the session topic (e.g. guilt, own suicidality). The screenplays of the protagonist’s monologue (played by an actor/actress) were developed with excerpts of the transcriptions from the focus groups. In order to ensure a balanced gender ratio, both men and women were represented equally in the testimonial videos. All testimonial videos follow the same structure: (1) How did the bereaved person experience e.g. feelings of guilt in the first days and weeks after the loss? (2) How did the bereaved person experience feelings of guilt over the course of time? (3) How did the bereaved person experience feelings of guilt today? The protagonists in the testimonial videos aim to function as role models in dealing with difficult emotions that occur after a suicide.

#### Treatment modules

The selection of the relevant themes for the intervention were based on the literature on grief or treatment of traumatized people [34], and on the results of the focus groups. Focus group interviews were analyzed and relevant themes were included in the treatment manual. Table 2 describes the complete content by session. The manual is based on cognitive behavioral principles and consists of (1) testimonial videos, (2) psychoeducation (e.g. grief, guilt, suicidality), (3) a guided group discussion about the topic of the session, and (4) individual tasks between the sessions (e.g. writing a farewell letter to the deceased).

**Table 2 Tab2:** The online group intervention: content and structure of each session

Number	Content	Structure
1	Introduction	▪ Group discussion: participants introduce themselves and the deceased ▪ Group guides introduce the program ▪ Individual writing assignment: set grief-related therapy goals
2	The suicide mode	▪ Video: a psychiatrist explains physical and psychological aspects of a suicide ▪ Group discussion on the suicide ▪ Individual writing assignment: circumstances of the suicide
3	My grief	▪ Psychoeducation: grief tasks [36] ▪ Group discussion on grief ▪ Individual writing assignment: relationship with the deceased person
4	Suicide as traumatic event	▪ Psychoeducation: symptoms of post-traumatic stress reactions ▪ Group discussion on symptoms ▪ Individual writing assignment: last hours of the deceased person
5	Meaning and the why-question	▪ Video: a wife talks about meaning-making after the suicide ▪ Group discussion on rumination ▪ Individual writing assignment: positive behavioral activation
6	Guilt	▪ Video: a mother talks about coping with guilt ▪ Group discussion on the functionality of guilt ▪ Individual writing assignment: letter to a friend
7	Own suicidality	▪ Video: a mother talks about coping with her own suicidality ▪ Psychoeducation: warning signs, coping strategies ▪ Group discussion on suicidality ▪ Individual writing assignment: crisis plan
8	Shame and stigmatization	▪ Video: a father talks about coping with stigmatization ▪ Group discussion on stigmatization ▪ Individual writing assignment: coping with stigmatizing reactions
9	To communicate the suicide	▪ Video: a brother talks about his way to communicate with others about the suicide of his sibling ▪ Psychoeducation: gender differences, communication styles ▪ Group discussion on communication ▪ Individual writing assignment: letter to a friend
10	Grief rituals	▪ Psychoeducation: grief rituals ▪ Group discussion on rituals ▪ Individual writing assignment: letter to the deceased person
11	Finding a new role in the future	▪ Video: a daughter talks about how she regained her life after the loss of her father ▪ Group discussion on coping with grief in the future and plans for the future ▪ Individual writing assignment: letter from the deceased person
12	Goodbye	▪ Group discussion about the intervention, changes and the group experience ▪ Individual writing assignment: goal attainment

#### The Internet tool

The webinar will be held using the Internet tool Adobe Connect®. Participants receive a link to log onto an online-seminar room and log in with a self-chosen user name. They are connected with each other via microphones and headphones but without video transmission. The visual transmission is disconnected to ensure increased anonymity for the participants. The participants are able to see PowerPoint slides or videos, which are part of the treatment program on their computer screen. The two group leaders can additionally access a list of names of all group members. There is also a chat option, which can be used by group participants or group leaders.

### Measures

#### Screening for eligibility criteria

The study coordinators will screen the participants for eligibility criteria using a semi-standardized clinical telephone interview. To exclude the presence of a current major depressive or manic episode, bipolar disorder, BPD, PTSD, or alcohol and substance misuse, the corresponding sections from the German version of the Structured Clinical Interview for DSM-IV [37] will be applied. The inter-rater reliabilities of the diagnoses vary between fair (e.g. agoraphobia) and excellent (e.g. PTSD, BPD) scores [38]. In addition, the German translations [39] of the Dutch Screening Device for Psychotic Disorder [40] and the Suicide Risk Assessment Interview [41] will be used to screen for acute schizophrenia and suicidality, respectively. All outcomes will be aggregated using sum scores, means, or standardized mean differences (i.e., Cohen’s *d* value for effect size) from baseline to post intervention and follow up. Thus, the timeframe will be 12 weeks from pre to post intervention, 3 months from pre to follow-up 1 and 3 months from pre to follow-up 2. The description of the specific outcome information (i.e. domain, measurement) can be found below.

#### Primary outcomes

The primary outcomes will be the level of suicidality and depression post treatment, and at 3-month and 6-month follow up. Suicidality and depression will be assessed using the following instruments.

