### Sample size

We based the power and sample size estimations in the current study on results from previous studies examining the effectiveness of online bereavement interventions [34]. Assuming a between-subject effect size of *d* = 0.80, power of 0.80, alpha of 0.05 (two-sided), and a dropout rate of 30%, the within-group sample size should be at least 52 participants. Hence, we aim to include 104 participants in total.

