### Statistical analysis

We will use repeated measures analysis of variance (ANOVA) to analyze the changes in the primary endpoint variables (suicidality and depression) and the secondary outcomes from baseline to post-measurement and the two follow-up assessments (3 months, 6 months), where the dependent variable will be the treatment condition (treatment group vs. waitlist control group). In addition, we will control for the baseline levels of depression and suicidality using analysis of covariance (ANCOVA). The predictor analyses will be conducted using the method of multiple regression. Interim analyses will be calculated to present first results before the study is finished. To control for differences between the online groups, multilevel analyses will be conducted to allow for variation between participants and online groups at level 1. The assignment to the study group (i.e., treatment, wait list) will be on level 2. Intraclass correlation will be tested to examine potential clustering effects of the online groups.

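### Each primary outcome gets two between-arm tests, a repeated measures ANOVA and a baseline-adjusted ANCOVA, and the protocol does not say which one decides

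*Protocol article*

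**What the plan says.** **Outcome.** Protocol article, Primary outcomes: "The primary outcomes will be the level of suicidality and depression post treatment, and at 3-month and 6-month follow up".

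**Analysis.** Protocol article, Statistical analysis: "We will use repeated measures analysis of variance (ANOVA) to analyze the changes in the primary endpoint variables (suicidality and depression"), running from baseline through post-measurement to both follow-ups. The next sentence adds: "In addition, we will control for the baseline levels of depression and suicidality using analysis of covariance (ANCOVA"). The same section plans multilevel analyses to allow for differences between online groups. It does not rank these analyses.

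**Effect size.** In the Measures section, under Screening for eligibility criteria: "All outcomes will be aggregated using sum scores, means, or standardized mean differences", the last of these being a Cohen's d "value for effect size) from baseline to post intervention and follow up". The Sample size section uses a different kind of d: "Assuming a between-subject effect size of *d* = 0.80".

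**The concern.** The outcome is worded as a level, the first test is on change, and the second is on a baseline-adjusted score. Followed literally, every primary scale yields at least two p-values for the comparison of arms. If one falls below 0.05 and the other does not, the protocol gives no ground for choosing between them, and either could be presented as the trial's result.

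The Blinding section does not close this gap. It conceals the arm labels until results are final, but an analyst who sees only coded arms still sees which model is significant.

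A smaller matter concerns Cohen's d. If it is taken from baseline to post within an arm, it includes natural recovery and regression to the mean. It then cannot be set against the between-subject d of 0.80 on which the trial is sized.

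**Working it through.** **Inputs from the protocol (Sample size).** d = 0.80, power 0.80, two-sided alpha 0.05, dropout 30%, 52 per arm, 104 in total.

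**The plan's own figure.** n per arm = 2(1.960 + 0.842)² / 0.80² = 24.5, so 25 (26 with the t-test). Dividing by 0.70 gives 36 (38) per arm, or 72–76 in total. The stated 52 per arm is not reproduced. That is a separate matter; I take 52 as given, so completers are 52 × 0.70 = 36 per arm.

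**Assumptions.** The protocol gives no correlation r between visits; I assume 0.5–0.7, equal for all pairs of visits. Scores are normal. Clustering by online group is ignored, so that only the tests are compared.

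**Step 1: precision in closed form (T0 and T12 only).** With the SD of a score set to 1, the SD that drives the comparison is √(2(1 − r)) for change and √(1 − r²) for ANCOVA. Their ratio, ANCOVA to change, is √((1 + r)/2), which is below 1 for every r below 1. With two visits, the repeated measures group-by-time test is the t-test on change. Power = Φ(d / (SD × √(2/36)) − 1.96), with √(2/36) = 0.2357.

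| d | r | Change | ANCOVA |
|---|---|---|---|
| 0.5 | 0.5 | 0.5/(1.000 × 0.2357) = 2.12; 56% | 0.5/(0.866 × 0.2357) = 2.45; 69% |
| 0.5 | 0.7 | 0.5/(0.775 × 0.2357) = 2.74; 78% | 0.5/(0.714 × 0.2357) = 2.97; 84% |
| 0.8 | 0.5 | 92% | 97% |
| 0.8 | 0.7 | 99% | 99.7% |

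**Step 2: the tests as planned, by simulation.** Scores were generated at T0, T12, T13 and T14 for 36 per arm, with the effect either maintained or lost at follow-up through waitlist catch-up. The 3-df group-by-time F test over four visits was compared with ANCOVA at T12.

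- d = 0.5: power is about 57–81% for the group-by-time test and 67–83% for ANCOVA, the lower figures at r = 0.5 and the higher at r = 0.7.
- d = 0.5: the two give opposite verdicts in about 16–32% of trials (the low end moves between 15% and 16% from run to run).
- No effect: at least one of the two is significant in about 8–9% of trials.
- No effect, T0 and T12 only: about 6–8%.
- d = 0.80: both exceed 90% power.

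**The case against.** The strongest reply has four parts.

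**One outcome, not several.** A reader might infer that the protocol gives four competing definitions of its endpoint: level, change, adjusted score and d. It does not. Only the Primary outcomes section defines the outcome. The Statistical analysis section lists models for it. With randomised arms, level, change and ANCOVA all target the same between-arm effect, and ANCOVA on the level or on the change gives the same treatment effect. This stands: the dispute is over the deciding test, not over what is estimated.

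**Cohen's d is a summary.** It has no test attached and no between-arm power of its own, and the phrase about baseline to post may only give the time frame. This stands too. The d point is a request for clarity.

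**The size can be overstated.** Adding a plain t-test on the level raises the false-positive rate to about 9–10%, but no such test is planned, so that figure does not apply. Part of the gap in Step 2 comes from the extra visits and degrees of freedom rather than the metric; hence the separate T0 and T12 figure. Under the planned last observation carried forward, about 52 per arm would be analysed. Treating those as full observations, power at d = 0.80 is at least 98%, and change and ANCOVA disagree in at most 2% of trials. A reader should therefore not conclude that the trial is underpowered at its design effect because of this choice.

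**A SAP may name the deciding model, and ANOVA followed by an added ANCOVA can be read as lead plus supplement.** Both are possible, and mere silence would be no finding. But the protocol itself sets two tests beside each other for an outcome that it words as a level, without ranking them. Its suggested lead, if order implies one, is the less precise of the two in the d = 0.5 settings examined.

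**Conclusion.** The point holds as an unranked pair of tests on each primary outcome. It does not hold as a conflict of estimands.

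The false-positive cost is about 8–9% instead of 5% per outcome if either test may count, or about 6–8% on T0 and T12 alone. The disagreement matters mainly at a medium effect, taken here as d = 0.5. That is relevant because the Discussion section claims adequate power for a medium effect. At d = 0.80 the choice makes little difference to power for correlations of 0.5–0.7. At an assumed r of 0.3, closed-form power at d = 0.80 is 82% for change and 94% for ANCOVA.

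These figures rest on an assumed correlation, 36 completers per arm, normal scores and no clustering. Whole groups of about 10 are randomised, so absolute power will differ from the values shown. Normality is doubtful for the Beck Scale for Suicide Ideation (range 0–38) in a sample that excludes acute suicidality, so the ANCOVA gain is not demonstrated for that scale. The lack of a named deciding test does not depend on any of these assumptions.

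**What to change.** In Statistical analysis, name one deciding analysis for each primary scale: the between-arm difference in score, adjusted for that same scale's baseline (ANCOVA), fitted within the multilevel model for online groups that the section already plans. Call the repeated measures ANOVA supportive.

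Which instruments and which time points are primary is a separate matter. This change should leave them as they are and should not drop a follow-up or a scale from primary status.

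In Measures, under Screening for eligibility criteria, state that the reported Cohen's d is the between-arm standardized difference, matching the between-subject d in Sample size. Any pre-post d is descriptive only.

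Cost: wording in two sections. Baseline scores are already collected at T0. The one downside is that the repeated measures ANOVA loses its place as the first-listed analysis.

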### Objectives

The main objective of this trial and the proposed online-group intervention is to reduce depression and suicidality in people bereaved by suicide. Secondary outcomes of the trial are prolonged grief disorder, posttraumatic stress disorder, anxiety, stigmatization, posttraumatic grief cognitions and social support. More precisely, our treatment-specific objectives are to determine whether:
The online group intervention significantly reduces symptoms of depression, suicidality, prolonged grief disorder, posttraumatic stress disorder, and anxiety after bereavement through suicide.The treatment effects (symptom reduction of primary and secondary outcomes) of the online group intervention are significantly greater than those of the control group after the end of treatment.

In addition, the study addresses the following process-specific research questions:
Which factors (such as age, sex, depression, severity of symptoms) are most likely to predict the effect of the treatment?To which extent does the relationship with the deceased (e.g. spouse, sibling, child, parent, friend) influence treatment outcomes in terms of grief and trauma symptoms?Which cognitive processes (such as stigma experience, guilt) influence the general psychopathology of study participants (e.g. depression, prolonged grief, trauma symptoms)?

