### Trial design

This study is a randomized control group design with two groups of equal sample size: the treatment group and the waitlist control group. The treatment group will receive treatment through the online group intervention immediately after registration. As a result of the focus groups with suicide survivors, the waitlist control condition was selected as the only one acceptable to the suicide survivors involved. A control that would not receive the intervention after the waiting period could reduce the motivation to participate.

This intervention is based on cognitive behavioral principles (psychoeducation, cognitive restructuring, dealing with difficult emotions such as guilt, shame, suicidality) and will take place once a week over a course of 12 weeks in total. The waitlist control group will receive the same intervention 12 weeks after registration. Participants will be randomly assigned to either group using computer-generated block-randomization. The study protocol was written in accordance with Statement Standard Protocol Items: Recommendations for Interventional Trials (SPIRIT) 2013 [33]; for the SPIRIT Checklist see Additional file 1).

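### The 3- and 6-month follow-ups are primary between-arm time points, but the waitlist is offered the intervention from week 12, so only the post-treatment contrast has an untreated control

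*Protocol article*

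**What the plan says.** All statements are in the protocol article.

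- **Primary outcomes:** "The primary outcomes will be the level of suicidality and depression post treatment, and at 3-month and 6-month follow up". Three time points are named as primary, with no order among them. The Secondary outcomes section uses the same three.
- **Statistical analysis:** a repeated measures ANOVA covers change "from baseline to post-measurement and the two follow-up assessments (3 months, 6 months" and, in the article's words, "the dependent variable will be the treatment condition (treatment group vs. waitlist control group". Treatment condition is evidently meant as the group factor, so a comparison of arms that includes both follow-ups is planned.
- **Trial design:** "The waitlist control group will receive the same intervention 12 weeks after registration". The intervention "will take place once a week over a course of 12 weeks in total". An untreated control was ruled out on purpose: "A control that would not receive the intervention after the waiting period could reduce the motivation to participate".
- **Symptom assessment:** T12 is the assessment at the end of the intervention. Further measurements come "after 3-month follow up (T13), and finally, after 6-month follow up (T14".
- **Screening for eligibility criteria:** the time frames given there put both follow-ups at 3 months from the pre-assessment, which does not agree with Symptom assessment.
- **Objectives:** the between-arm objective is that effects "are significantly greater than those of the control group after the end of treatment". It does not mention follow-up.

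**The concern.** A waitlist serves as a control only while it waits. Here the wait ends at week 12, yet two of the three primary time points come later and are still analysed as treatment against waitlist.

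The interpretation of the main result is at stake. A reader who takes all three time points as tests of the intervention will expect the arms to differ at each. If the intervention works and the waitlist catches up, the arms should converge at follow-up. That convergence could be reported as an effect that was not maintained. If the arms do differ at follow-up, the difference describes receiving the intervention earlier or later, not receiving it or going without. Neither result answers the question in the Objectives section.

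**Working it through.** **1. Timeline.** Inputs: immediate start for the treatment arm, 12 weekly sessions, and waitlist start 12 weeks after registration (Trial design); T13 and T14 counted after T12 (Symptom assessment). Taking 3 months as 12 to 13 weeks, T13 is at week 12 + 12 = 24 to 12 + 13 = 25. T14 is at week 12 + 24 = 36 to 12 + 26 = 38. The waitlist is treated from week 12 to about 12 + 12 = 24.

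| Time point | Week | Treatment arm | Waitlist arm | Contrast |
|---|---|---|---|---|
| T12 | 12 | end of treatment | untreated | treated vs. untreated |
| T13 | about 24–25 | 3 months after | just treated | immediate vs. delayed |
| T14 | about 36–38 | 6 months after | about 3 months after | immediate vs. delayed |

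**2. Other readings of the calendar.** If the waitlist's T13 and T14 run from the end of its own treatment, its members are still treated at both points. If the time frames under Screening for eligibility criteria are taken literally, both follow-ups fall at about week 13. They would coincide with each other and nearly with T12, which contradicts Symptom assessment and a 6-month follow-up.

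**3. Size at each time point.** The Sample size section assumes d = 0.80 and attaches it to no time point. (Its 52 per group is not reproduced from its inputs: a t-test gives 26 per group, and 26/0.7 gives 38. That is a separate matter.) Assume that the waitlist gains the same benefit once treated and that effects do not decay. The expected arm difference is then 0.80 at T12, 0.80 − 0.80 = 0 at T13, and 0 at T14. With 52 × 0.7 = 36.4, about 36 evaluable per arm, a two-sided 5% t-test and no clustering, power for a single-time-point comparison is:

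| Arm difference d | Power |
|---|---|
| 0.80 (T12) | 0.92 |
| 0.40 (partial catch-up) | 0.39 |
| 0.20 | 0.13 |
| 0 (full catch-up) | 0.05, the test's alpha |

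**4. The group-by-time interaction.** Under compound symmetry with unit variance and correlation ρ, its noncentrality is (n/2) × SS / (1 − ρ). SS is the sum of squared deviations of the arm differences around their mean over time.

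- Waitlist catches up, differences (0, 0.8, 0, 0): mean 0.2, SS = 3 × 0.2² + 0.6² = 0.12 + 0.36 = 0.48.
- Control stays untreated and the benefit lasts, differences (0, 0.8, 0.8, 0.8): mean 0.6, SS = 0.6² + 3 × 0.2² = 0.36 + 0.12 = 0.48.

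The two are equal. With n = 36 and ρ = 0.5 (an assumption), noncentrality is 18 × 0.48 / 0.5 = 17.28 and power is 0.95 for both patterns. For baseline and T12 alone, SS = 2 × 0.4² = 0.32, noncentrality is 18 × 0.32 / 0.5 = 11.52 and power is 0.92. The ordering is the same at 26, 36 and 52 per arm and at ρ from 0.3 to 0.7. The interaction therefore keeps its power. It also cannot tell these two very different patterns apart.

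**The case against.** Several points on the other side have force.

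- **Dilution of the test.** A reader might average the post-baseline differences, (0.80 + 0 + 0)/3 = 0.27, and conclude that the planned analysis sees only a third of the effect. The documents do not support this. That average would describe an overall post-baseline group effect, which the Statistical analysis section does not specify. The interaction does not average, and the calculation shows no loss of power under this scenario.
- **The follow-ups are not worthless.** One might infer that they estimate no treatment effect at all. That goes too far: they remain randomised comparisons of immediate with delayed intervention. What they cannot give is intervention against none.
- **The Objectives section limits the claim.** Its between-arm objective is set at the end of treatment and agrees with the remedy, so it is not in error. It does not, however, remove the follow-ups from the Primary outcomes or Statistical analysis sections.
- **Fig. 1 and Table 1 are not shown, and a separate analysis plan may exist.** The waitlist's exact calendar is unknown. But post-treatment follow-ups counted from either arm's schedule leave a treated control, and the concern is with time points that the article fixes, not with detail left out.
- **ANCOVA and multilevel models are planned.** They adjust for baseline and online group. They cannot restore a control that has been treated.

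The limitations in the Discussion mention the waitlist only as not being an active comparator. Loss of the control at follow-up is not acknowledged.

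**Conclusion.** The point holds and the text is wrong as written. Of three primary time points, only T12 compares treated with untreated participants. At T13 and T14 the planned contrast is immediate against delayed intervention, and under equal benefit without decay its expected size is near zero instead of 0.80. The harm lies in interpretation: a working intervention could be read as not maintained, and a significant four-time-point interaction would not identify T12 as its source. The T12 contrast is unaffected, and no loss of power is shown for the interaction test.

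The structural conclusion rests on the waitlist starting at week 12 as planned and on follow-ups counted after T12. The Discussion allows for scheduling delays, which could move the start. The sizes rest further on equal benefit, no decay, about 36 evaluable per arm, compound symmetry and no clustering, and are illustrations only.

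**What to change.** - **Primary outcomes:** name BSS and BDI-II at T12, before the waitlist starts treatment, as the only time point for the confirmatory between-arm test.
- **Secondary outcomes:** limit comparisons with an untreated control to T12 in the same way.
- **Statistical analysis:** restrict the confirmatory comparison of arms to baseline and T12. Label T13 and T14 as secondary, analysed as within-arm maintenance or explicitly as immediate versus delayed intervention, with no claim against an untreated control.
- **Screening for eligibility criteria and Symptom assessment:** reconcile the follow-up timings, and state from which event each arm's follow-ups are counted.
- **Objectives:** no change needed.

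The cost is wording, settled before the between-arm analysis. No participants or visits are added. The trial gives up a between-arm claim at follow-up that the design cannot support.
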